**Fig 4 pone.0272101.g004:**

Flow diagram of MERTIL *for Parents* professional data collection timeline.

#### Parents

During the study pilot phase, recommended parents who arrive at the MERTIL *for Parents* website will be welcomed to the pilot study. Recommended parents will be invited to read more about the study. If they consent, these parents will provide their contact details, agreeing to view the study’s explanatory statement and, if they wish, to complete the content form. Once complete, the pre-program parent survey will appear. Parents who arrive at the website, but who were not recommended to the program by their MCH practitioner, will be informed that the program is currently not widely accessible, but will be available to all following the current testing phase.

The brief parent surveys before, immediately after, and at 3-months follow-up comprise two sections: i) close-ended questions, and ii) open-ended questions. Upon completion of Survey 1 (10-minutes), participants can access the MERTIL *for Parents* program. Participants will have program access for 2 months from consent completion. Immediately upon MERTIL *for Parents* program completion, Survey 2 will be available (5-minutes). Three-months after completion of MERTIL *for Parents*, a follow-up survey (10-minutes) will be sent to explore sustained change. As needed, survey reminders will be sent via email at 7- and 14-days after the initial survey. If participants do not complete surveys after these communication bids, no further contact will be made. Consenting parents will participate in a qualitative interview, to further identify their program lived experience, as well as program strengths and weaknesses. See Fig 5 for an outline of parent data collection points.

**Fig 5 pone.0272101.g005:**

Flow diagram of MERTIL *for Parents* parent data collection timeline.

During this research and piloting phase, MERTIL *for Parents* will be free of charge to recommended parents and caregivers who choose to participate in the research. Following this piloting phase and program refinement, MERTIL *for Parents* will be made broadly available.

### Measures

Our primary outcome will be to determine the efficacy of MERTIL *for Parents* in enhancing socioemotional development. Secondary outcomes include evaluating the feasibility of implementing MERTIL *for Parents* within Victorian and New South Wales MCH services.

#### Parents

*Baseline and three-month post-program questionnaires*. To evaluate program efficacy, participants will complete identical self-report measures pre-program and at three-months post-program (see Table 3); noting that demographic questions would have been completed pre-program and will not be repeated. Program efficacy questions will be both quantitative and qualitative in nature. Program efficacy will not be assessed at program exit as not enough time would have elapsed for meaningful parent change. All included measurement items were derived where possible from complete validated scales, single items from validated scales, and/or items from established Australian longitudinal cohort studies (i.e., Australian Temperament Project; Longitudinal Study of Australian Children); however, some study-generated items were also developed. Table 3 displays outcomes and associated measures that will be used to evaluate MERTIL *for Parents* pre- and post-program. For additional information, contact the first author.

**Table 3 pone.0272101.t003:** Pre- and post-MERTIL *for Parents* self-report outcomes and measures.

Outcome	Measure (reference)	Number of items
Study eligibility	Study-generated items	3
Demographics (including trauma items)	Study-generated items	19 (1 optional)
Parent-child relationship	Maternal Postnatal Attachment Scale [35]	4
	Perinatal Emotional Growth Index [36]	1
	Measures from longitudinal cohort studies [i.e., ATP; 37, LSAC; 38]	3
Child emotional functioning	Measures from longitudinal cohort studies [i.e., ATP; 37, LSAC; 38]	1
	Brief Infant-Toddler Social and Emotional Assessment [39]	5
Relational attunement	Parental Reflective Functioning Questionnaire [40]	5
Parenting experience & practices	Measures from longitudinal cohort studies [i.e., ATP; 37, LSAC; 38]	6
	The Parent Coping Scale [41]	1
Parent distress	Patient Health Questionnaire-4 [42]	2
Social support	Maternal Social Support Scale [43]	3
Professional help-seeking amenability	Study-generated item	1
Intimate partner safety	Family Law Detection of Overall Risk Screen [44]	2
Parent conflict	Measures from longitudinal cohort studies [i.e., ATP; 37, LSAC; 38]	2 (optional)
Qualitative questions	Study-generated items	2
**Total**		**60–63 (3 optional)**

*Note*. Light grey shading = Items not completed at the three-month follow-up survey; ATP = Australian Temperament Project; LSAC = Longitudinal Study of Australian Children.

In addition to the above items, in the pre-program and three-months post-program questionnaires, parents will be asked open-ended free-text response questions relating to the program. Pre-program questions will cover hopes for learning, and three-month post-program feedback questions will include items on program components that parents found most useful.

Embedded within this study is an internal program evaluation consisting of multiple-choice questions and open-ended text-response questions. Specifically, upon program exit (data collection time two) parents will be asked to complete a five-minute survey relating to program usability and program satisfaction. Example questions asked include: i) *How useful was the program for you*, *as a parent of a young child*? and ii) *What was most helpful about* MERTIL *for Parents*? This will be sent to parents via email with an attached secure link.

Parents’ online program usage data will also be automatically collected via the MERTIL *for Parents* website. This will record program engagement and completion elements such as i) program completion rates, ii) number of access occasions, iii) program components most/least accessed.

#### Practitioners

After practitioners hear from the parents they recommended MERTIL *for Parents* to, practitioners will be asked to complete a brief mixed methods online survey, allowing insight into practitioners’ perceptions of the program. Questions will include: i) *Would you recommend MERTIL for Parents to future parents*? ii) *Would you recommend colleagues encourage future parents to participate in MERTIL for Parents*? iii) *From your perspective*, *does MERTIL for Parents fill a current preventative health gap*? and iv) *Are there any existing gaps in the MERTIL for Parents program*? For each question response, options will be ‘yes’ or ‘no’, and then practitioner participants will be asked to expand upon their answer with free text.

### Focus groups

To further examine the feasibility and efficacy of MERTIL *for Parents*, four online Zoom-recorded focus groups will be held upon program completion. There will be two practitioner and two parent focus groups held. A subsample of volunteer practitioner and parent participants will join the optional focus groups with each group consisting of 4–6 parents or practitioners. A semi-structured interview schedule will guide focus group discussions. All focus groups will be audio recorded to allow for later transcription and analysis.

#### Practitioners

Example focus group questions will include: i) *Could you tell us about your MERTIL for Parents experience*? ii) *What was most relevant to you*? iii) *Can you see yourself in the future encouraging suitable parents to participate in MERTIL for Parents as a first intervention step*? and iv) *What are the long-term and short-term implications of programs such as MERTIL for Parents*?

#### Parent

Example focus group questions will include: i) *Could you tell us what it was like to participate in MERTIL for Parents*? ii) *Since completing MERTIL for Parents*, *what*, *if anything*, *has changed in your thinking*, *or feeling*, *or in your behaviour as a parent*? iii) *In MERTIL for Parents*, *what was most relevant to you*? and iv) *Would you recommend MERTIL for Parents to other parents*?

### Program data management

All professional and parent survey data will be disseminated through Moodle, an online learning management system stored on a secure server, with data transferred securely for analyses. All study data and participant information will be stored securely as per the criteria required by the La Trobe University Human Ethics Committee.

### Data analysis strategy

#### Quantitative

All statistical analyses will be conducted using the software IBM SPSS Statistics [45]. Descriptive statistics will be generated to identify professional and parent population characteristics and to evaluate parent and professional program perceptions. To determine parenting change in dyadic attachment, relational function, maternal mental health, from pre-program to three-months post-program, inferential statistics will be used (i.e., univariate, bivariate, and multivariate analyses) such as t-tests, chi-squared analyses, ANOVA, and regression analyses.

#### Qualitative

*Focus groups*. All parent and professional focus group interview data will be audio-recorded, transcribed verbatim, and deidentified. Thematic and content analysis will be used to identify themes and sub-themes from practitioners and parent transcript responses [46].

*Free-text surveys responses*. For practitioner and parent free-text survey responses, thematic analysis will also be used to identify response themes and sub-themes.

### Data collection commencement

Pilot field studies, including recruitment and data collection, will commence in March 2023 with data collection concluding in June 2023.

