### Design

MERTIL *for Parents* will be examined via a parallel armed (i.e., practitioners and parents), uncontrolled, mixed methods, repeated measures study design. Practitioners will complete two assessments (pre-parent recruitment and three-month post-program) and parents will complete three assessments (pre-program, program exit, and three-month program follow-up). All practitioners and parent data collection and completion will be conducted independently and in parallel.

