### Procedure

#### Practitioners

Following informed consent, practitioners will attend a 120-minute web-based information and training session on MERTIL *for Parents*. This session will provide a study overview to promote program and pilot study familiarisation. Immediately following this session, practitioners will be asked to complete an online survey to report their first impressions of MERTIL *for Parents* regarding factors such as perceived program content, length, and suitability.

Practitioners will be asked to make contact with parents they refer to the program, within two weeks of recommending MERTIL *for Parents*. This follow-up contact will be via an informal face-to-face chat, phone call, or email. Once practitioners have recommended the program to parents, they will be invited to complete a second survey. This final practitioner survey will assess views on program usability, impactfulness, engagement, and ideas for program refinement and wider implementation. Online focus group interviews will follow to elaborate on survey responses, assess practitioner views and experiences of the program, potential barriers to implementation, and to identify further uses and applications of MERTIL *for Parents*. These elements will ensure MERTIL *for Parents’* co-designed nature endures. See Fig 4 for the professional data collection flow diagram.

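### The June 2023 close of data collection does not fit the three-month follow-up: only parents who finish the program by about 30 March can be sent the primary-outcome survey in time

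*Protocol article*

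**What the plan says.** The section on data collection commencement gives one window for everything: "Pilot field studies, including recruitment and data collection, will commence in March 2023 with data collection concluding in June 2023". It gives no closing date for parent recruitment.

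The parent procedure sets the length of each parent's path. "Participants will have program access for 2 months from consent completion". Then: "Three-months after completion of MERTIL *for Parents*, a follow-up survey (10-minutes) will be sent to explore sustained change". Where needed, "survey reminders will be sent via email at 7- and 14-days after the initial survey". The Design section gives the same schedule: "parents will complete three assessments (pre-program, program exit, and three-month program follow-up". It also places the practitioners' second assessment at three months post-program.

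Under Measures, efficacy comes first: "Our primary outcome will be to determine the efficacy of" the program. The parent measures are taken before the program and at three months, and the exit survey is excluded as an efficacy time point: "Program efficacy will not be assessed at program exit as not enough time would have elapsed for meaningful parent change".

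Before any parent is referred, "practitioners will attend a 120-minute web-based information and training session" and complete a first survey.

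**The concern.** The stated window is shorter than the longest path the plan allows a parent, and only about one month longer than the shortest. The measurement at the end of that path is the only post-program efficacy measurement, so a parent whose three-month date falls after the close contributes a baseline and an exit satisfaction survey but nothing to the primary comparison.

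Two things are at stake. The first is the number of before-and-after pairs, and so the power. The second is who supplies them: parents referred earliest who finished fastest. They may differ from other parents in motivation, service type or need, and a before-and-after change in them may not describe the recruited sample. The margin between 199 and 480 is justified in the protocol by participant attrition. Loss to the calendar uses up the same margin before any parent drops out.

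**Working it through.** **Inputs.** Window March to June 2023 (Data collection commencement). Access up to 2 months from consent, survey 3 months after completion, reminders at 7 and 14 days (Procedure, Parents). Required 199 parents, effect .20, p < .05, 80% power, target 480 (Sample size/power calculation). No recruitment pattern is given, so the consent and completion patterns in step 3 are assumptions.

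**1. The plan's own figure.** A paired t-test, two-sided 5%, standardised change 0.20, noncentral t: power is 79.97% at n = 198 and 80.2% at n = 199. The stated 199 is reproduced exactly. As a share of the target, 199/480 = 41.5%.

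**2. Calendar.**
- Window, counted generously from 1 March to 30 June inclusive: 122 days.
- Shortest path: 0 + 3 = 3 months. Longest: 2 + 3 = 5 months, plus up to 14 days.
- Longest path from 1 March: program finished 1 May, survey 1 August, last reminder 15 August.
- Latest completion for a survey by 30 June: 30 June − 3 months (92 days) = 30 March. Leaving 14 days for reminders: 16 March.

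So 122 − 92 = 30 days are usable for consent and completion together, or 16 days with the full reminder cycle.

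**3. Parents due by 30 June, before any dropout.** Let consent be uniform over R days and time to finish uniform over A days.
- Same-day completion: share = 30/R.
- A up to 30 days: share = (30 − A/2)/R.
- A = 61 (the full access period): share = 30²/(2 × R × 61) = 450/(61R).

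| Consent spread over | Completion | Share due | Of 480 | Power at that n |
|---|---|---|---|---|
| March–June (R = 122) | same day | 30/122 = 25% | 118 | 58% |
| March–June | over 2 months | 450/7442 = 6% | 29 | 18% |
| March–April (R = 61) | same day | 30/61 = 49% | 236 | 86% |
| March–April | within 2 weeks | 23/61 = 38% | 181 | 76% |
| March–April | over 2 months | 450/3721 = 12% | 58 | 32% |
| March only (R = 31) | same day | 30/31 = 97% | 465 | 99% |
| March only | within 2 weeks | 23/31 = 74% | 356 | 96% |
| March only | within 30 days | 15/31 = 48% | 232 | 86% |
| March only | over 2 months | 450/1891 = 24% | 114 | 56% |

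**4. If the full 14-day reminder cycle must also fit.** Replace 30 days by 16. March–June, same day: 16/122 = 13% (63). March only, same day: 16/31 = 52% (248). March only, within 2 weeks: (16 − 7)/31 = 29% (139). These are lower limits on what is collected, since a parent who answers the first invitation needs no reminder.

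**5. Closing date that fits the schedule.** If consent runs to 30 June: + 2 months = 30 August; + 3 months = 30 November; + 14 days = 14 December 2023.

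**The case against.** The best defence is that two months is a ceiling. The main component is a 40-minute video, and the section on program engagement says it may be finished in one sitting, so the 1 August case is the extreme. Nor does the article say that recruitment runs to the end of June. If all 480 parents consented in March and finished within 30 days, or consented over March and April and finished the same day, more than 199 would still be due in time.

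That stands, and it limits what can be claimed. A reader might infer that most, or nearly all, of the three-month data will be lost. The documents do not support that as a fact, because it depends on a recruitment pattern they do not give. A reader might also infer that no three-month outcome will exist under a June close. That is not so either: the outcome would be reduced and selective, but not absent.

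The favourable cases still ask a great deal. Recruitment itself only starts in March, practitioners must consent, be trained and complete a survey first, and parents are approached at service visits. The figures above also allow for no dropout, although the target was raised from 199 to 480 because dropout is expected.

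Reading June as the end of recruitment or baseline only does not help. The sentence names recruitment and data collection and then says when data collection ends, and the three-month survey is data collection.

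**Conclusion.** The contradiction holds and needs no assumption: a permitted path of up to five months plus 14 days does not fit a window of at most 122 days, and nothing else in the article resolves it. Any parent who finishes after about 30 March falls outside the window for the only post-program efficacy measurement.

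The size of the loss does need assumptions. Under uniform consent and completion and no dropout, it runs from almost none (97% due) to almost all (6% due). The 199 needed for 80% power is reached only with very early recruitment and fast completion, and the parents retained would be the earliest and fastest completers.

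The sample size of 199 is correct and not affected. The article cannot show whether the closing date is misstated or the follow-up schedule was not meant to be completed for everyone. Because the primary outcome depends on the answer, this must be settled.

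**What to change.** Reconcile the section on data collection commencement with the Design, parent Procedure and parent Measures sections. State two dates: close of parent recruitment, and close of data collection. Set the second to last parent consent + 2 months + 3 months + 14 days, which is about mid-December 2023 if consent runs to the end of June. Move the practitioners' three-month assessment to match.

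If the June close is fixed, state a recruitment and program-completion cut-off of about 30 March for the three-month outcome, restate the expected number of parents with three-month data and the resulting power, and limit the efficacy claim to that early-completing subset.

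The cost is a longer calendar and a timeline amendment. The number of parents and the measures need not change.

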## Discussion

### Limitations and challenges

While this study is innovative, we foresee several program content and delivery method limitations: Firstly, it is possible that the brief self-guided content of MERTIL *for Parents* may not provide adequate content information and support (i.e., program dose too low). Second, as frontline services, practitioners may lack the time in session to explain and recommend parents to participate in MERTIL *for Parents*, due to competing demands and scheduling pressures. Third, as the study population pertains only to practitioners and parents located in Victoria and New South Wales, Australia, generalisability concerns will be present for interstate Australian and international populations. Fourth, as all MERTIL *for Parents* content is housed online, this may exclude those who lack the technology or skills to participate, especially as on-demand technical support will not be available for live participant trouble shooting. Further, because of this study’s non-randomised sampling strategy, cause-effect relationships cannot be drawn. That is, parents’ socioemotional outcome changes cannot be causally inferred by their MERTIL *for Parents* participation. Finally, as with all research, there is a risk that attrition rates may be high. All parent data will be self-report in nature, and interpretation of findings will therefore be subject to these limitations.

### Strengths and opportunities

There are multiple strengths to the present study: First, the mixed methods design of this study allows for greater understanding of the program’s impact compared with either qualitative- or quantitative-only designs. Second, diversity of parent demographics and needs will be ensured through recruitment of participants from both Universal and Enhanced MCH services, in both metropolitan and regional locations. Third, socioemotional-specific content may fill an important gap in the available online parenting program market. Fourth, the program’s reach is expected to be wide due to the online delivery method. Finally, strong completion is expected due to i) the program’s brief nature, ii) the engaging, non-judgemental, and supportive program content; and iii) the contribution of MCH nurses, infant mental health experts, and parents in co-designing the program.

### Conclusion

This study will examine implementation feasibility and efficacy of an evidence-based, online, universal, self-directed parenting program, MERTIL *for Parents*. Multi-informant data from parents and varied practitioners will inform future iterations of MERTIL *for Parents* and universal online relational programs.
